### Aims of the TIRED study

We designed a multicentre RCT to test the efficacy of either GET or CBT compared to Usual Care (UC) in reducing fatigue (primary outcome) in incurable cancer patients receiving systemic treatment with palliative intent. In addition, the efficacy on improving quality of life and functional impairment will be studied. All outcomes will be assessed at baseline, and at 14, 18 and 26-weeks post-randomisation. We will assess the efficacy of GET or CBT compared to UC directly post-intervention at 14-weeks post-randomisation, which is the primary endpoint of this study. In addition, we will determine whether the expected intervention effects are sustained at follow-up assessments (18-weeks and 26-weeks post-randomisation). Furthermore, if GET and/or CBT are efficacious in reducing CRF, we will perform a mediation analysis to test if the changes in four variables (i.e., physical activity, physical fitness, self-efficacy with respect to fatigue, and/or fatigue catastrophising) mediate the reduction in fatigue.

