### Outcomes

Outcome measures and data collection time points are listed in Table 3. The primary endpoint of this study is the post-intervention assessment (T1), 14 weeks after randomisation. Primary and secondary outcomes will be measured at baseline (T0), post-intervention (T1) and follow-up (T2, T3). Proposed mediators will only be assessed at T0 and T1.

**Table 3 Tab3:** Data collection time point of all outcome measures and proposed mediators

Concept	Questionnaire	Measurement time points			
		T0	T1	T2	T3
Socio-demographics	Self-report questionnaire	X			
Medical characteristics	Medical chart review	X	X		
Primary outcome:					
Fatigue severity	CIS *fatigue severity*	X	X	X	X
Secondary outcomes:					
Fatigue	EORTC QLQ-C30 *fatigue*	X	X	X	X
Quality of life	EORTC QLQ-C30 *global health status*	X	X	X	X
Functional impairments	SIP	X	X	X	X
	EORTC QLQ-C30 *emotional functioning*	X	X	X	X
	EORTC QLQ-C30 *physical functioning*	X	X	X	X
Proposed mediators:					
Physical activity	Actigraphy during 12 consecutive days	X	X		
Physical fitness	6MWT	X	X		
Self-efficacy	SES	X	X		
Fatigue catastrophising	FCS	X	X		

*T0* baseline (pre-intervention), *T1* post-intervention/UC (14 weeks post-randomisation), *T2* first follow-up assessment (18-weeks post-randomisation), *T3* s follow-up assessment (26-weeks post-randomisation)

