### Statistical analyses

The statistician who will perform data analyses will be blinded for intervention allocation. To test the efficacy of both interventions compared to UC, an ANCOVA will be performed for each intervention with *fatigue severity* (CIS-fatigue) at T1 as dependent measure, condition as fixed factor and CIS-fatigue screening score as covariate [47]. Missing data is a common problem in palliative care research and is also anticipated in our study as a result of deteriorating health or because the patient has died. Data will be primarily analysed on complete case basis, i.e. only data from evaluable participants with a T1 assessment will be used. The *p*-level is adjusted to 0.025 to account for the two primary analyses, i.e., GET versus UC and CBT versus UC. When statistically significant differences between GET versus UC and/or CBT versus UC are found, additional sensitivity analysis accounting for all randomised participants will be done to explore the impact of missing data. Several methods of imputation are available and the choice will depend on the actual circumstances of missing data. We will record the causes of missing data and careful considerations will be given to which imputation procedure should be used.

In addition, ANCOVA will be performed for the secondary outcomes (*fatigue, quality of life, and functional impairments*), with baseline score (T0) on the dependent measure as covariate. In these exploratory analyses a *p*-level of 0.05 will be used. Longer-term follow-up effects at T2 and T3 will also be tested using ANCOVA, with baseline score (T0) on the dependent measure as covariate. Again, in these explorative analyses a *p*-level of 0.05 will be used. No sensitivity analysis will be done, as the power for follow-up analyses will be limited due to the expected significant amount of attrition.

Mediation analysis will be conducted to explore the possible underlying mechanisms of the expected reduction in fatigue severity (CIS-fatigue) brought on by GET and CBT at T1. Following recommendations of Preacher and Hayes (2008) [48], we will perform multiple mediation analysis using bootstrapping to test the mediating effect of four potential mediators (i.e., changes in *physical activity, physical fitness, self-efficacy with respect to fatigue, and catastrophising in response to fatigue*). We will only perform multiple mediation analysis when there is a significant effect of one or both interventions compared to UC.

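### Sensitivity analysis at T2 and T3 is ruled out because attrition will limit power, which leaves the sustained-effect aim open to bias from selective dropout

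*Protocol article*

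**What the plan says.** All references are to the protocol article.

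- **Aims of the TIRED study:** "we will determine whether the expected intervention effects are sustained at follow-up assessments", at 18 and 26 weeks after randomisation.
- **Statistical analyses, follow-up method:** "Longer-term follow-up effects at T2 and T3 will also be tested using ANCOVA, with baseline score (T0) on the dependent measure as covariate". These tests use a 0.05 level and are labelled explorative.
- **Statistical analyses, follow-up missing data:** "No sensitivity analysis will be done, as the power for follow-up analyses will be limited due to the expected significant amount of attrition".
- **Statistical analyses, analysis set:** "Data will be primarily analysed on complete case basis, i.e. only data from evaluable participants with a T1 assessment will be used". This wording covers T1. No other set and no imputation is named for T2 or T3.
- **Statistical analyses, cause of missing data:** it "is also anticipated in our study as a result of deteriorating health or because the patient has died".
- **Statistical analyses, T1:** if a primary comparison is significant, "additional sensitivity analysis accounting for all randomised participants will be done to explore the impact of missing data".
- **Outcomes and Table 3:** CIS-fatigue is collected at T0, T1, T2 and T3.

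**The concern.** The sentence is a positive decision with a stated reason, not a detail left to another document, and the reason does not support the decision. Attrition does two separate things. It widens confidence intervals, and if it is selective it shifts the estimate. The plan cites the first to justify not looking at the second.

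The protection also runs the wrong way round. T1, with 30% attrition planned, gets a conditional sensitivity analysis on all randomised participants. T2 and T3, where losses can only accumulate, get none. Entry requires a treatment plan based on survival of six months or more, which is about the time of T3, so deaths before T3 are foreseeable.

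Whether an effect is sustained is judged by comparing estimates across visits. If each visit rests on those still responding, a change in effect cannot be told apart from a change in who is measured. The T1 score is already collected and is plausibly the best available predictor of later fatigue, but the T2/T3 model does not use it.

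**Working it through.** **1. The plan's own figure.** 51 / (1 − 0.30) = 72.9, rounded up to 73 per arm; 3 × 73 = 219. This reproduces exactly. The SD is not stated. Inverting 51 per arm (difference 6, two-sided alpha 0.025, power 0.80, t-test) gives a standardised difference of 0.618, so SD = 6 / 0.618 = 9.7.

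**2. Is power at follow-up necessarily limited?** Power ≈ Φ(δ / (SD × √(2/n)) − 1.96), with SD 9.7 and alpha 0.05. Only the 30% is in the article (for T1); the other rates are assumptions.

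| Attrition | n per arm | Power, 6 points | Power, 3 points |
|---|---|---|---|
| 30% | 51 | 88% | 35% |
| 40% | 44 | 83% | 31% |
| 50% | 36 | 75% | 26% |
| 60% | 29 | 65% | 22% |

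Power is low only if attrition is heavy or the effect has shrunk. In neither case does that bear on bias.

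**3. Possible bias under dropout that depends on T1 fatigue.** The assumptions are SD 9.7, correlations T0–T1 0.3, T0–T3 0.3 and T1–T3 0.6, and 30% of those seen at T1 lost by T3. The log-odds of loss rise by 1 per SD of T1 fatigue. The true T1 effect is −6 unless stated, and negative values favour the intervention. The simulation used 300,000 per arm, so the table shows bias rather than noise.

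Two estimators were compared:
- **Plan:** regress T3 on arm and T0 among those seen at T3.
- **Likelihood using T1:** regress T1 on arm and T0 in everyone with T1 (arm coefficient a). Regress T3 on arm, T0 and T1 in those seen at T3 (arm coefficient b, T1 coefficient c). The estimate is b + c × a. This matches a repeated-measures likelihood fit when dropout is monotone.

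| Dropout depends on T1 fatigue in | True T3 effect | Plan | Using T1 |
|---|---|---|---|
| both arms equally | −6 | −5.58 | −6.01 |
| both arms equally | −3 | −2.55 | −2.99 |
| both arms equally | 0 | +0.46 | +0.03 |
| both equally, no effect at T1 either | 0 | −0.01 | 0.00 |
| usual care only | −3 | −1.68 | −3.00 |
| intervention only | −3 | −4.14 | −3.03 |

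With equal mechanisms the bias is 0 to about 0.5 points, against the intervention; at half the slope it was 0.13. With dependence in one arm only it is about 1.1 to 1.4 points, and the sign depends on which arm.

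**4. Precision.** With 51 per arm at T1, true T3 effect −3 and T1–T3 correlation 0.6, the plan's estimator had mean −2.57 and SD 2.12; using T1 gave −2.97 and 2.08. Root mean squared error is √(2.12² + 0.43²) = 2.16 against √(2.08² + 0.03²) = 2.08, about 4% lower. The gain is mainly in bias.

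**5. Dropout that depends on the unseen T3 score.** With a true effect of −6, the plan's estimator gave −5.21 and the one using T1 gave −5.44. Both are biased, so changing the model alone is not enough.

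**The case against.** The strongest reply is that little is at stake. T2 and T3 are labelled explorative, and the primary endpoint is T1. With equal mechanisms the bias of up to 0.5 points is under a quarter of a standard error near 2.1, and small beside the 6 points the plan calls clinically relevant. In that case it understates persistence rather than inventing it. Arm-specific dropout need not do much harm either: one simulation with other assumed values (73 per arm, 45–53% seen at T3) gave 5.95 against a true 6. The plan also has safeguards. Reasons for missed T1, T2 and T3 assessments will be recorded and analysed (Refusal of study participation and study dropout), and follow-up is completed at home by web or on paper.

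Much of this stands. It limits the point to the follow-up aim and rules out any firm claim about magnitude. It does not rescue the stated reason. The recorded reasons are meant to inform generalisability and do not test the T2/T3 estimates.

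A reader might infer more than the article supports:

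- **That it prescribes separate complete-case analyses at T2 and T3.** Complete case is spelled out for T1 only. For follow-up it is the natural implication, since no joint model or imputation is described.
- **That it expects dropout to follow earlier measured fatigue, leaving ever healthier participants.** It names worsening health and death; the link to T1 scores is an assumption made here.
- **That a repeated-measures model removes survivor bias.** It is unbiased above because dropout was simulated to depend on observed T1. It does not settle what fatigue means for participants who have died.

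**Conclusion.** The point holds in this limited form. The reason given for omitting sensitivity analysis at T2 and T3 is wrong, and the sustained-effect aim is left open to bias from selective dropout. The primary T1 conclusion is unaffected by it. The article supplies no follow-up attrition, SD or correlations, so neither size nor direction can be derived from it. Under the assumptions shown, the bias is about 0 to 0.5 points towards understating the effect with equal mechanisms, and about 1 to 1.4 points either way when dropout depends on fatigue in one arm only. The documents do not support saying that the plan will overstate persistence, or that its follow-up results will be materially wrong. They support saying that, as planned, nobody could tell. The change is worth making because it is cheap, but it is not critical to the trial.

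**What to change.** 1. Delete the sentence that rules out sensitivity analysis.
2. Estimate the T2 and T3 contrasts from one repeated-measures likelihood model over T1, T2 and T3, with arm × visit and T0 score × visit terms and an unstructured covariance. Include every participant with any post-baseline score. The primary T1 test stays as planned.
3. Keep the visit-wise ANCOVA as a supporting analysis.
4. Add at least one missing-not-at-random sensitivity analysis for T2 and T3, for example delta-adjusted imputation over a range fixed in advance, whether or not the results are significant.
5. State how deaths are handled in the effect being estimated at T2 and T3.
6. Report dropout and deaths by arm and visit.

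The cost is revised analysis wording and a little more programming, with no new data. The downside is that the main follow-up model rests on missing at random and does not by itself resolve truncation by death, which is why items 4 and 5 belong with it. The gain in precision will be small.

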### Ethical approval

The study protocol has been reviewed and approved by the Research Ethics Committee of our University-affiliated hospital (CMO Arnhem-Nijmegen, reference no. 2012/240) and the local Ethics Committees of the participating hospitals (Hospital Gelderse Vallei, Máxima Medical Center, Isala Hospital, Canisius-Wilhelmina Hospital, Hospital Pantein, Jeroen Bosch Hospital, VieCuri Medical Center, Academic Medical Center). The study is registered in the Dutch Trial Registry (reference no. NTR3812, date registered: January 23, 2013).

## Discussion

Fatigue is one of the most prevalent symptoms compromising quality of life of incurable cancer patients receiving systemic treatment with palliative intent. Graded exercise and cognitive behavioural interventions seem promising in reducing fatigue severity based on their effectiveness in disease-free cancer patients and patients receiving cancer treatment with curative intent. To our knowledge, the TIRED study will be the first RCT determining the efficacy of GET and CBT compared to UC in reducing severe fatigue in incurable cancer patients receiving systemic treatment with palliative intent.

Recruitment of participants started in January 2013. Thus far, identifying potential study participants via nurses and oncologists for this palliative care RCT has been challenging. One common barrier for recruitment in palliative care research known from the literature is professional gatekeeping [49]. A recent systematic review by Kars et al. (2015) explored reasons for gatekeeping in palliative care research, the professionals’ perception that study participation would be too burdensome for the patients was the most reported reason [50]. Yet, we recently demonstrated that 93% of incurable cancer patients that completed a fatigue-screening questionnaire during cancer treatment with palliative intent wanted to be informed by a researcher about available interventional studies for fatigue [51]. Other important reasons for gatekeeping reported by Kars et al. (2015) included health carers’ lack of time, complicated study procedures, or study procedures that interrupt usual care processes [50]. These issues have also been observed in our study and as a result we have simplified our study procedures. For example, we originally aimed to screen for the presence of severe fatigue during a nursing consultation before the first line of systemic treatment with palliative intent began. However, nurses indicated that patients often raise several important time-consuming treatment-related questions, which hampered nurses from administering the fatigue screening. Therefore, we amended the study protocol by also allowing patients to be screened for fatigue at consultations further on during treatment. Moreover, we initially aimed to include a homogeneous sample of patients with incurable breast or colorectal cancer. Then again, poor recruitment rates during the first year, made us broaden our inclusion criterion regarding cancer type. Finally, we have extended our research collaboration with three hospitals to nine hospitals in total. All study protocol amendments have been reviewed and approved by the Research Ethics Committee of our University-affiliated hospital and the local Ethics Committees of the participating hospitals.

In conclusion, the TIRED study will provide information on the efficacy of GET and CBT compared to UC in reducing severe fatigue in incurable cancer patients, as well as on the mediators of any observed intervention effects. Other important outcome measures will include quality of life and functional impairments. If proven efficacious, one or both interventions might be offered as part of UC for this often overlooked and understudied patient group.

### Status of the trial

The TIRED-study started in January 2013 and patient recruitment is ongoing.

## Abbreviations

1RM: One-Repetition Maximum
6-MWT: Six-Minute Walking Test
CBT: Cognitive Behaviour Therapy
CIS: Checklist Individual Strength
EORTC-QLQ-C30: European Organisation for Research and Treatment of Cancer-Quality of Life Questionnaire-Core 30
FCS: Fatigue Catastrophising Scale
GET: Graded Exercise Therapy
HRR: Heart Rate Reserve
RCT: Randomised Controlled Trial
SES: Self Efficacy Scale
SIP: Sickness Impact Profile
UC: Usual Care
